**Fig. 2 Fig2:**
[figure not shown]
Causal model for patients enrolled in the trial. Legend: Arrows depicted in green (solid line), red (long-dashed line) and blue (short-dashed line) represent causal relationships of one variable on another. The presence of green arrows will be examined in hypothesis 1. The presence of blue arrows (mediation effects) and red arrows (moderation effects) will be examined in an exploratory analysis

### Aim 2

To improve self-reported HL knowledge, skills, and behavior of the participating GPs.

### Hypothesis 2

A HL training program for GPs targeting CRC screening will improve GPs’ self-reported HL knowledge, skills, and behavior compared to baseline (collected prior to training).

### Aim 3

To understand how to promote the intervention’s sustained use and rapid implementation, using the Normalization Process Theory (NPT).

### Hypothesis 3

In accordance with NPT, a brief online HL training program will be acceptable to GPs and likely to be sustained as long as they perceive the intervention to be valuable (i.e., converting to a higher screening rate), easily integrated in their workflow (for the patient facing component of the intervention) and agree that it is important to address HL among underserved patients eligible for CRC screening.

### Design

We will use a multicentric two-arm (intervention versus control) randomized controlled cluster trial design (see Fig. 3). The cluster unit is the GP or the GP office (if more than 1 GP per office agrees to participate). We will target underserved areas in the following regions in France: Provence Alpes Côte d’Azur, Auvergne-Rhône-Alpes, Occitanie and Île-de-France using the European Deprivation Index (EDI) to recruit GPs working in areas with high deprivation (EDI of 4 or 5) [36]. We will follow a community-based participatory research (CBPR) approach throughout this project. We are applying CBPR principles by involving patients in all aspects of the trial, and developing effective methods for facilitating routine patient engagement (for example, with a community advisory board) [37–39]. CBPR requires partnership and shared responsibility among patients, clinicians, administrators, and nurses, and has a higher likelihood of success and implementation [38]. We have established partnerships with 10 members of the public eligible for screening in underserved areas, other professional stakeholders and organizations that support those patients (La Ligue Nationale Contre le Cancer, Santé Publique France, La Fondation ARCAD (Aide et Recherche en Cancérologie Digestive)) and the coordinators of the CRCDCs of the four regions targeted by the study. A health economic assessment will assess the cost effectiveness of the intervention.

**Fig. 3 Fig3:**
[figure not shown]
CONSORT flow diagram

### Conceptual model

We will use the framework developed by Cooper et al. to design and evaluate interventions designed to eliminate healthcare disparities [40]. This framework will guide the adaptation of the intervention, and will inform the design and conduct of the trial. Strategies that are likely to improve outcomes in underserved populations and reduce disparities need to be multi-factorial and address: personal factors (e.g., language, literacy, HL, education/income), as well as clinician-level factors or mediators (e.g., communication style, HL awareness, understanding of the barriers and facilitators to communicating clearly with patients of lower HL and activating/empowering them), and system-level factors. The intervention we propose to evaluate will address all three levels as follows:
Provide accessible, evidence-based and balanced information (following plain language and HL principles) to people of lower socioeconomic position and their families/caregivers about CRC screening to improve screening uptake and other outcomes (knowledge, patient activation) (personal factors);Address HL by training GPs in HL principles and CRC screening (clinician-level factors or mediators);Standardize the information provided to all patients and improve patient activation to improve screening uptake, overall health and disease management, and the proportion of patients who complete a colonoscopy after a positive FIT test (system-level factors) in the four selected regions.

In parallel, we will also be guided by the Medical Research Council (MRC) framework for the evaluation of complex healthcare interventions [41]. We have successfully used those frameworks before [42].

### Participants

#### Inclusion criteria

Participants will be invited to participate and included if:
they are aged between 50 and 74 years old (age group eligible for CRC screening);they are eligible for CRC screening, have health insurance, and are seen by a participating GP in one of the four included regions;they are able to complete a questionnaire in French either alone or with help from a caregiver or relative, or in another language assisted by an interpreter.

Individuals with an intellectual disability will be included as long as they are able to complete a questionnaire alone or with help from a caregiver or relative.

#### Exclusion criteria

We will exclude patients not eligible for CRC screening and those whose mental health status precludes participation in the study as determined by the participating GP or a qualified staff member.

### Setting

The study will be conducted in underserved geographical areas in and around the cities of Toulouse, Lyon, Paris and Marseille. We will use the European Deprivation Index (EDI) to identify GPs in disadvantaged areas (EDI 4 or 5) [36].

### GP recruitment

To recruit GPs, we will first use a purposive sampling approach to include a balance of male and female GPs, practicing alone and in medical centers, in each region. GP work addresses will be coded against the EDI to establish if their practice covers a geographically disadvantaged area (EDI 4 or 5). GPs will be approached by email or telephone and given information about the trial. If this approach fails, we will transition to a convenience sampling approach, using contacts in our research network. Confirmation of participation will be by email and further contact details obtained. GPs will be randomly allocated to the control or intervention arm prior to the intervention training process, 2 months before patient recruitment begins. If a participating GP leaves their practice or decides to leave the trial, we will recruit another GP and assign him or her to the same arm.

### Participation and recruitment procedures for trial entry

Within the 4 regional areas, clinical research assistants (CRAs) will work in collaboration with recruited GPs. Participants will be approached in primary care medical centers or at individual GPs’ offices by their doctor, a resident (“interne”), or another member of the medical center. Clinical staff will confirm eligibility (see Fig. 3) and obtain verbal consent. Once participants are recruited, CRAs will re-confirm verbal consent over the telephone and check whether they are able to complete the questionnaires alone or if they need assistance.

### Ethical approval, consent and recruitment strategies

The trial has received approval from the local research ethics committee, the Comité d’Ethique de la Recherche (CER) at the University of Toulouse III Paul Sabatier, France (ref 2021–349, dated 8th March 2021). Eligible participants will be asked to read a brief information sheet written in plain language or have a resident, mediator/patient navigator or other member of medical staff read the information out loud to them. This is particularly relevant since participants targeted by the trial are likely to have lower HL and lower textual literacy. According to the French health research classification, the ethics committee’s requirement for consent for this study requires participants’ verbal consent only or ‘non-opposition’ consent. Participants recruited by an intervention GP will be given a pictorial brochure about CRC screening and asked to watch a 3-min video on a tablet before exiting the primary care center/GP’s office. Participants recruited by a GP in the control arm will discuss the trial and CRC screening in their usual way.

One week after (T1), the CRA will call participants and offer to conduct a standardized telephone interview where the questions will be read out loud to them. Whenever possible, T1 data collection will be carried out in a single phone call. If the participant does not answer the first telephone call, the CRA will make three further attempts to contact them and leave up to three voice messages. CRAs will verify telephone contact details with the recruiting GP practices. Given participants are likely to have lower HL, this is the best strategy to maximize retention and minimize participant burden and missing data.

One year after (T2), CRAs will call participants for the follow-up assessment and offer to conduct a further standardized telephone interview. As with T1, attempts to verify contact details and to call the participant several times will be made.

### Intervention

We will translate and adapt (using a translation procedure adapted from TRAPD) an intervention previously developed and evaluated in a randomized controlled trial conducted in the US to address HL and improve CRC screening [33]. This intervention combined a 2-h HL and CRC screening training targeting GPs and a patient level intervention consisting of a short brochure and video. To maximize generalizability and implementation, we will develop a 2 h e-learning HL training in French and a one-hour booster session similar to the previous trial’s intervention [33]. The first hour will be an online course that will primarily include didactic teaching using videos. The second hour will consist of a c-MOOC (Connectivist – Massive Online Learning Course), an online classroom model, where all participating GPs in the intervention group can interact with each other and with a trained facilitator from our team, experienced in HL training ([name]). This interactive session will build on the content provided in the initial didactic session. The c-MOOC is based on a learner-driven dialogue where participation, discussions and reflection on the content presented are the intended focus. It will also include small group discussions and role-playing sessions focused on empowering GPs to discuss CRC screening effectively with their patients. A 1-h c-MOOC booster training session will be held 6 months later. During this session, GPs will receive data on their screening uptake rates over the previous 6 months, a reminder of practical strategies to communicate with patients with lower HL skills in busy, high-volume primary care practices. They will also have the opportunity to engage in small group discussions. Each GP in the intervention arm will receive 150 euros for completing the first 2-h learning training (1 h didactic learning + 1 h c-MOOC) and 75 euros for completing the booster session (1 h c-MOOC).

The patient-facing intervention (brochure and video) will follow key plain language and HL principles to translate evidence-based information in to content that all patients can understand. Images and simple text will be used to facilitate understanding and promote informed choice and patient-centered care for all patients, irrespective of HL levels. To promote accessibility among underserved populations whose primary language may not be French, we will use existing systems already embedded in our teams in each region and additional interpretation services as relevant.

### Outcome measures

#### Primary outcome measure

The primary outcome measure is CRC screening uptake assessed 1 year after the initial recruitment consultation (T2) by self-report questionnaire (see Table 1). Each CRCDC, in collaboration with the health insurance body (CPAM) in each region, will also provide data on CRC screening uptake at 6 months (for feedback to GPs in the intervention arm) and 1-year post enrollment.

**Table 1 Tab1:** Outcome measures and data collection timepoints for patients

Outcome measures	Timepoints	
	(T1) One week after the primary care consultation where CRC screening is discussed	(T2) 1 year after the CRC screening consultation
Number of eligible patients identified and successfully enrolled	**X**	
Number of patients enrolled who receive the patient-facing intervention	**X**	
Discontinuation rate		**X**
CRC screening uptake (primary outcome) with self-report item		**X**
Screening intention (1 items)	**X**	
Knowledge of CRC screening (2 items)	**X**	**X**
Patient activation (13 items)	**X**	**X**
Health literacy (7 items)	**X**	
EPICES (11 items)	**X**	
SURE (4 items)	**X**	
Was the questionnaire completed alone? (1 item)	**X**	**X**
Demographics (9 items)	**X**	
**Total number of self-report items per timepoint**	**48**	**17**

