#### Secondary outcome measures

We will use standard telephone interviews with patients to collect secondary outcomes measures 1 week (T1) and 1 year (T2) after the initial recruitment consultation. These include: screening intention (1 item, assessed at T1), knowledge about the test instructions and the objectives of the screening test, (2 items, assessed at T1 and T2), patient activation (13 items- assessed at T1 and T2). We will use a validated short form patient activation measure, already available in French [43, 44]. We will assess HL using the Newest Vital Sign [45] (6 items) and the “single item literacy screener” [46] (1 item) (both assessed at T1). We will evaluate decisional conflict with SURE (4 items, assessed at T1) [47]. Finally, we will assess the proportion of patients who complete colonoscopy after a positive FIT test result within 1 year (collected by each regional coordination center in collaboration with the health insurance body). We will also collect socio-demographic information: age, gender, comorbidities, mother tongue, marital status, length of time living in France, educational attainment, income bracket, whether help was required to complete the questionnaire, any previous screening tests completed and the EPICES (Évaluation de la Précarité et des Inégalités de santé dans les Centres d’Examens de Santé), a validated measure of deprivation and social health in French, with 11 self-reported items (assessed at T1) [46].

Secondary outcomes for GPs will include a translated 12-item questionnaire assessing self-reported HL knowledge, skills, and behavior, collected prior to the intervention training and 1 year post training for GPs in both trial arms. We will also collect demographic information: age, gender, type of practice (GP practicing alone or in a medical center), year of medical training and participation in (and details of) a lump-sum participation package, ROSP (la rémunération sur objectifs de santé publique), an incentivized public health initiative. Tables 1 and 2 summarize the outcome measures and data collection timepoints.

**Table 2 Tab2:** Outcome measures and data collection timepoints for GPs

Outcome measures	Timepoints	
	Immediately before the health literacy training	1 year after the health literacy training
Health literacy knowledge, skills, and behavior (12 items)	**X**	**X**
Demographics (6 items)	**X**	
**Total number of self-report items per timepoint**	**18**	**12**

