### Sample size and power calculation

We plan to recruit at least 32 GPs across 4 regions. Based on Ferreira et al.’s trial findings, to detect a 15% difference between the control and intervention arm in CRC screening uptake, with an intra-cluster correlation (ICC) of 0.004 and a 25% attrition rate, a sample size of 1000 people eligible for screening is required [33]. This 15% difference is conservative. The ICC is based on previous studies similar to this trial. Each clinician will be expected to recruit approximately 32 patients, or as many eligible patients as possible if they cannot recruit 32, over the course of 1 year. On average, French GPs have about 300 eligible patients for CRC screening each year. Targeting 32 patients of about 300 represents just under 10%, which is achievable.

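### The primary outcome is a single one-year self-report item with 25% attrition expected, although screening-centre and insurer data on uptake will also be obtained: a risk of bias rather than of lost power

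*Protocol article*

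**What the plan says.** All references are to the protocol article.

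- **Primary outcome measure:** "The primary outcome measure is CRC screening uptake assessed 1 year after the initial recruitment consultation (T2) by self-report questionnaire". Table 1 repeats this as "CRC screening uptake (primary outcome) with self-report item", collected at T2 only.
- **Ethical approval, consent and recruitment strategies:** at one year, "CRAs will call participants for the follow-up assessment and offer to conduct a further standardized telephone interview". The self-report is therefore taken by telephone.
- **Primary outcome measure, next sentence:** the regional screening centres, working with the insurer, "will also provide data on CRC screening uptake at 6 months (for feedback to GPs in the intervention arm) and 1-year post enrollment".
- **Secondary outcome measures:** completion of colonoscopy after a positive FIT within one year is "collected by each regional coordination center in collaboration with the health insurance body".
- **Sample size and power calculation:** the trial is sized "to detect a 15% difference between the control and intervention arm in CRC screening uptake". The allowances for clustering and for loss of patients are given as "with an intra-cluster correlation (ICC) of 0.004 and a 25% attrition rate".
- **Missing data:** the need for multiple imputation will be looked into. The records are not named as a source for patients without a T2 answer.
- **Blinding:** the research assistants who collect the primary outcome are said not to know allocation, and patients are said to be probably unaware of their arm.

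**The concern.** The result of the trial rests on one answer given by telephone a year after the consultation. Such an answer is open to recall error and to the wish to give the approved reply. It is also missing for anyone who cannot be reached, and being reachable may be related to having been screened.

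If misreporting or outcome-related non-response differs by arm, it enters the estimated effect directly. If misreporting is equal in the arms, it shrinks a true effect. The arms are not alike in exposure, because only intervention patients are given the brochure and shown the video.

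The plan already arranges for one-year uptake data from bodies that do not depend on reaching the patient or on the patient's memory.

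**Working it through.** **1. Is it one item?** The T2 column of Table 1 holds uptake 1 + knowledge 2 + activation 13 + completed alone 1 = 17, the printed total. Uptake is a single item.

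**2. Are the records likely to be patient-level?** The article does not say so. Two statements point that way:
- One-year data are timed from enrolment, which is a patient-specific clock.
- The colonoscopy outcome requires knowing which enrolled patients had a FIT, which FITs were positive, and who then had a colonoscopy. The FIT record is an intermediate step in an outcome already planned from the same bodies.

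Against this, the one stated use of the six-month data is feedback of rates to GPs, which could be supplied in aggregate. Patient-level data are a strong inference that needs confirming.

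**3. The plan's own figure.** The section says that "a sample size of 1000 people eligible for screening is required". Alpha, power and control uptake are not given, so this cannot be tested strictly. Assume control 30.5% (the national uptake in the Background), 45.5% in the intervention arm and two-sided 5%, with design effect 1 + 31 × 0.004 = 1.124 and division by 0.75 for attrition. The total is then 494, 656 or 811 for 80%, 90% or 95% power. The stated 1000 exceeds these but is not shown to be wrong, and nothing below depends on it.

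**4. Patients without a primary outcome.** 32 GPs × 32 patients = 1024. 25% of 1024 = 256, leaving 768.

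**5. Power and precision** (same assumptions, ICC 0.004 from the article):

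| Source | Analysed | Design effect | Effective n per arm | Power for 15 points | Detectable difference, 80% power |
|---|---|---|---|---|---|
| Self-report | 768 | 1 + 23 × 0.004 = 1.092 | 384/1.092 = 352 | 98.5% | 10.1 points |
| Records, all enrolled | 1024 | 1 + 31 × 0.004 = 1.124 | 512/1.124 = 456 | 99.7% | 8.8 points |

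At an ICC of 0.05, which is my assumption and not in the article, power is 83% with self-report and 87% with records. The gain in precision is modest in both cases.

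**6. Reporting error (all error rates assumed).** Observed rate = p × sensitivity + (1 − p) × (1 − specificity).
- *Over-reporting in the intervention arm only, no true effect.* False difference = (1 − 0.305) × f, where f is the share of unscreened patients who say they were screened.
  - f = 5%: 0.695 × 0.05 = 3.5 points
  - f = 10%: 7.0 points
  - f = 15%: 10.4 points

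  The chance of a falsely significant result in favour of the intervention, with 768 analysed, is about 17%, 49% and 82%.
- *Equal error in both arms.* The true difference is multiplied by (sensitivity + specificity − 1). With sensitivity 95% and specificity 95%, 90% or 80%, 15 points becomes 13.5, 12.8 or 11.3 (power 96%, 93% or 85%).

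**7. Outcome-related non-response (response rates assumed, overall 75%, true uptake 30.5%).** Observed rate = p·r₁ / [p·r₁ + (1 − p)·r₀], where r₁ and r₀ are the response rates of screened and unscreened patients.
- r₁ = 80%, r₀ = 72.8%: 0.244/0.750 = 32.5%, up 2.0 points
- r₁ = 85%, r₀ = 70.6%: up 4.1 points
- r₁ = 90%, r₀ = 68.4%: up 6.1 points

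A shift of this kind biases the comparison mainly to the extent that the pattern differs by arm.

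**The case against.** The strongest case for the plan has several parts.

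- **Blinding.** Outcome collectors are stated to be blind and patients probably unaware of their arm. This makes differential reporting less likely, and that part stands. It does not exclude it: a blind interviewer cannot stop a patient over-reporting, only one arm receives the materials, and under Statistical analysis all participants are asked at T1 whether they received the intervention. T1 is a telephone interview held by a research assistant, so the answer may reveal the arm.
- **The materials.** A reader might infer that they push patients to claim a test. The article describes them as accessible, balanced and supportive of informed choice, so that is not supported. What remains is the difference in exposure between arms.
- **Availability of records.** A reader might infer that a dated record is already assured for every patient who misses the T2 call. The article does not say this. It has to be confirmed.
- **Timing.** A reader might infer that self-report cannot separate tests before and after enrolment. The item's wording is not shown, patients must be eligible for screening at entry, and earlier tests are recorded at T1. The point is unproven.
- **Missing data.** Attrition that differs by arm is not predicted in the article, and loss explained by observed covariates can be handled by adjustment or imputation. Only loss that depends on the outcome itself would remain.
- **Detail left elsewhere.** An SAP or full protocol may say how the records support the self-report. Silence on that is not the finding. The finding is the choice of primary source, which the article does fix.

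**Conclusion.** The concern holds as a design choice that leaves avoidable bias. It is neither a contradiction nor an arithmetic error. As written, about 256 of 1024 patients would have no primary outcome at the planned attrition, and the other 768 would be classified by an unverified answer. Data on the same outcome from the screening centres and insurer are expected at the same time point.

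The size of the bias is unknown. The +3.5 points for 5% one-sided over-reporting shows the mechanism and is not an estimate for this trial. It rests on an assumed error rate and on national uptake of 30.5%, which may not apply in deprived areas.

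A reader might infer that the trial is underpowered because of the attrition. The figures do not support that: with the article's ICC, power for 15 points is 98.5% with self-report and 99.7% with records, under the assumed control rate and two-sided 5%.

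The case for changing the source depends on the records being patient-level and dated. The colonoscopy outcome strongly suggests that they are patient-level, but the article states neither property.

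**What to change.** 1. Confirm with the screening centres and the insurer that one-year uptake will be supplied per enrolled patient, with the date of the test, including for patients who complete neither interview, and that the consent obtained covers this.
2. If so, define the primary outcome as record-based CRC screening uptake from the enrolment consultation to 12 months, for all enrolled patients regardless of T1 or T2 completion.
3. Keep the meaning of uptake as it is now and state which tests count. Changing the source should not silently narrow the endpoint to FIT alone.
4. Make the self-report item a secondary or sensitivity outcome, and report its agreement with the record by arm.
5. If patient-level dated records cannot be had, say so, justify self-report as primary, and prespecify whatever validation against the centre data is possible.

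**Cost.** A change of wording, plus confirmation of a data flow that appears largely planned. The sample size need not change. Tests done outside the programme and not recorded may be missed, and it should not be assumed that this is equal in the arms. The self-report sensitivity analysis can examine it. The change should be made before T2 data accrue.
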